# Summary of trial protocol submitted and approved by the University of Sydney’s Human Research Ethics Committee

## Aims:

The aims of the study are threefold: (1) to investigate the impact of an online planning tool on unhealthy snacking behaviour at one-month follow-up; (2) to compare this effect amongst higher and lower health literacy groups, and; (3) to investigate possible mediating factors or predictors of the effectiveness of the intervention, and how this relates to health literacy.

## Hypotheses:

1. Participants using the volitional help sheet will have higher maintenance self-efficacy scores than participants using the detailed planning intervention, and participants in these groups (averaged) will have higher scores than participants in the passive control group.

2. Participants using the volitional help sheet will have lower unhealthy snacking scores than participants using the detailed planning intervention, and participants in these groups (averaged) will have lower scores than participants in the passive control group.

3. Change in behaviour will be mediated by maintenance self-efficacy

4. The effects of planning tool will be moderated by health literacy. It is hypothesised that the volitional help sheet will be more useful (i.e. reduce unhealthy snacking to a greater extent) for people with lower healthy literacy than the detailed planning intervention

## Research plan including duration of the study and/or timeline:

It is estimated that recruitment and data collection will take three months (including a month interim period between the first and second survey). The study will be conducted via two online surveys (Qualtrics). The first survey will take approximately 20mins and the second approximately 10mins.

Participant characteristics including sex, age range and inclusion/exclusion criteria (if relevant):

A sample of 435 eligible participants will be recruited through SSI, a ‘software-as-a-service’ company. They will recruit potential participants from their existing database until 435 eligible participants are identified based on screening questions to assess eligibility: at least 30 years of age, and sufficiently able to understand health-related information in English. Furthermore, in order to facilitate the involvement of people likely to be of lower health-literacy, half (50%) of all participants will have no university degree. Other than that, potential participants will be recruited to reflect the general population in terms of sex, age, cultural background, employment status, income.

## The intended sample size with a justification, and/or the participant sampling/selection strategy (as relevant to your study):

The intended sample size is approximately 435 participants. Piloting the survey will allow for a more definite sample size to be determined. Eighty-seven participants randomized to each group (totalling 261 participants) will yield ~90% power to detect moderate effect sizes (Cohen’s f = 0.25, corresponding to ANOVA effects and interaction as small as ?p 2 = 0.06) in the primary outcomes (maintenance self-efficacy scores; unhealthy snacking scores) and any secondary analyses, assuming a Bonferroni-adjusted two-sided alpha of 0.017 (allowing for four planned comparisons, and a correlation between the two primary outcome measures of ~ 0.25). Additionally, just under 50% additional cases will be recruited to account for potential missing values or attrition, totalling 435 participants (i.e., 145 per group).

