### Details of how data will be analysed:

Randomisation will be tested using MANOVA (multivariate analysis of variance), to ensure similarity across the three groups of participants in terms of demographic and other descriptive characteristics at baseline. The effect of the planning tools (volitional help sheet; detailed planning; information sheet) will be assessed using ANCOVA (analysis of covariance), controlling for: baseline values, age, sex, and language spoken at home. Orthogonal planned contrasts will be used to test if the volitional help sheet is superior to the detailed planning intervention, and if both of these interventions are superior to the passive control intervention (information sheet) on the primary outcomes. Secondary analyses will include exploring possible mediation of behavioural change by maintenance self-efficacy by using bootstrapping procedures as outlined in Preacher and Hayes (2008; BehavResMethods 40: 879-891). The potential moderating effect of health literacy on the efficacy of planning tools will be explored by examining the interaction of intervention and health literacy in ANCOVA.

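### The ~90% power matches a 2-df F test, but the primary outcomes are tested by two 1-df contrasts that cannot both have that power at f = 0.25 before covariate adjustment

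*Protocol*

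**What the plan says.** The sample-size section of the protocol states that "Eighty-seven participants randomized to each group (totalling 261 participants) will yield ~90% power to detect moderate effect sizes". The effect is given as Cohen's "f = 0.25, corresponding to ANOVA effects and interaction as small as" a partial eta squared of 0.06, "assuming a Bonferroni-adjusted two-sided alpha of 0.017 (allowing for four planned comparisons" and a correlation of about 0.25 between the two primary outcomes). The same sentence extends the claim to both primary outcomes and to every secondary analysis. Recruitment is then raised to 145 per group to cover missing data and attrition.

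The analysis section uses ANCOVA, adjusted for baseline value, age, sex and language spoken at home. For the primary outcomes it says: "Orthogonal planned contrasts will be used to test if the volitional help sheet is superior to the detailed planning intervention", and adds a second contrast of the two planning tools against the passive control. The Hypotheses section has the same structure for each primary outcome: help sheet better than detailed plan, and, for snacking, "participants in these groups (averaged) will have lower scores than participants in the passive control group". Two contrasts on two outcomes give the four planned comparisons for which alpha is set.

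The protocol gives no group means, standard deviation, pairwise effect size, baseline correlation or contrast-specific power.

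**The concern.** Cohen's f for three groups measures the overall spread of the means. It does not say how that spread divides between the two contrasts that decide the primary hypotheses. The help sheet versus detailed plan contrast also uses only two of the three arms, 174 of the 261 participants. A power figure for the overall spread therefore does not carry over to each contrast, although the alpha in the same sentence is set for those contrasts.

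The stake is interpretation. If help sheet and detailed plan do not differ significantly, a reader would set that result against a stated 90% power that the calculation does not establish for that comparison.

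The extension to all secondary analyses raises a smaller problem of the same kind. One of them is a bootstrapped indirect effect, and Cohen's f does not define the size of an indirect effect.

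**Working it through.** **Inputs from the protocol (sample-size section).** 87 per group, three groups, N = 261; f = 0.25; two-sided alpha 0.017. **Assumptions, not in the protocol.** d = 0.5 as the two-group equivalent of f = 0.25 (d = 2f); equally spaced means; a baseline–outcome correlation r.

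**1. Reproduce the stated figure.** Noncentrality λ = N·f² = 261 × 0.0625 = 16.31.
- Three-group omnibus F (df 2, 258): 90.4%. The smallest n per group that reaches 90% is 87.
- 3×2 interaction (df 2, 255): 90.3%.
- A 1-df contrast with f = 0.25 on all 261: 94.8%.
- Two arms of 87 at d = 0.5: 81%.

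Only the 2-df effects match ~90% at the stated alpha. That the calculation was for a 2-df test is inferred from this match; the text does not name the test.

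**2. Noncentrality of each contrast** (differences in SD units, 87 per arm, error df 258).
- Help sheet versus detailed plan: λ₁ = d₁² × 87/2 = 43.5·d₁².
- Average of both tools versus control: λ₂ = d₂² / (1/174 + 1/87) = 58·d₂².
- The contrasts are orthogonal, so λ₁ + λ₂ = 16.31 at three-group f = 0.25.

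**3. What 90% requires.** A 1-df test at alpha 0.017 with 258 error df needs λ = 13.61 for 90% power. Two such contrasts need 2 × 13.61 = 27.2, against 16.3 available. Both cannot reach 90% under any pattern of means, before covariate adjustment.

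**4. How the available 16.31 may divide at f = 0.25.**

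| Pattern of means | Help sheet vs detailed plan | Average vs control |
|---|---|---|
| Even split, λ = 8.16 each | 67% | 67% |
| Equally spaced (d₁ = 0.306, λ₁ = 4.08; d₂ = 0.459, λ₂ = 12.23) | 35% | 86% |
| Detailed plan equal to control (d₁ = 0.53) | 86% | 35% |
| Control midway between the tools (d₁ = 0.61) | 95% | about 2% |
| Both tools equal (d₁ = 0) | about 2% | 95% |

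For equal spacing with step δ, f² = 2δ²/3, so δ = √(1.5 × 0.0625) = 0.306.

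**5. Each contrast at an assumed d = 0.5.** λ₁ = 43.5 × 0.25 = 10.88 gives 81%. λ₂ = 58 × 0.25 = 14.5 gives 92%.

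**6. Difference detectable with 90% power.** d₁ = √(13.61/43.5) = 0.56. d₂ = √(13.61/58) = 0.48.

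**7. Baseline adjustment.** A correlation r multiplies λ by 1/(1 − r²). For help sheet versus detailed plan:

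| r | d = 0.5 | Equally spaced (d = 0.306) |
|---|---|---|
| 0 | 81% | 35% |
| 0.3 | 85% | 39% |
| 0.5 | 92% | 47% |
| 0.7 | 99% | 67% |

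For both contrasts to reach 90% at f = 0.25, covariates must explain at least 1 − 16.31/27.21 = 40% of the variance (r about 0.63), and the means must also split the noncentrality evenly.

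**The case against.** The strongest reply has four parts.

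- **The planned analysis is ANCOVA with the baseline value.** At r = 0.5 the head-to-head contrast has 92% power at d = 0.5, above the stated figure. This stands: the 81% is a pre-adjustment figure. But the protocol gives no correlation and the power sentence claims no gain from adjustment, so the shortfall can be neither confirmed nor dismissed.
- **Average versus control is adequately powered at d = 0.5 (92%).** This also stands. At that effect size the shortfall lies in the head-to-head contrast alone.
- **f = 0.25 might be meant for each effect separately.** A 1-df contrast would then have 94.8% power, which is not the ~90% stated, and 87 would not be the number required.
- **More people are recruited than the calculation needs.** If all 145 per group were analysed, λ would be 16.31 × 145/87 = 27.2, just enough for 90% on both contrasts if split evenly. Equally spaced means would still leave the head-to-head contrast at 58%. The protocol assigns the extra recruits to missing data and attrition, and its power claim is made for 87.

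Some stronger readings are tempting but not supported. A reader might take 35% as the power under the protocol's own hypotheses. Those give no spacing and do not order the detailed plan against control, so power for this contrast at f = 0.25 runs from about 2% to 95%. A reader might also infer that 90% for the head-to-head contrast contradicts the hypotheses. It does not: at d₁ = 0.56 the remaining noncentrality is 16.31 − 13.61 = 2.71, so the two-tool average still beats control by √(2.71/58) = 0.22 SD. The hypotheses concern that average, although the second contrast then has only about 23% power.

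**Conclusion.** The concern holds as a mismatch between the powered test and the primary tests; the arithmetic behind the ~90% is correct. At three-group f = 0.25, alpha 0.017 and 87 per group, before covariate adjustment, no pattern of means gives both contrasts 90% power. This conclusion needs no assumption about spacing. It rests on reading f = 0.25 as a three-group effect, which is inferred from the numerical match.

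The size for a single contrast does depend on assumptions. At d = 0.5 it is 81% for help sheet versus detailed plan and 92% for average versus control. With equally spaced means it is 35% and 86%. Baseline adjustment at r = 0.5 raises the head-to-head figures to 92% and 47%.

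It would go too far to say that the ~90% fails for every secondary analysis. The interaction with health literacy is a 2-df test in the 3×2 design and reproduces at 90.3%; only the mediation analysis lacks a basis. Nor does this point show that alpha should be 0.0125. That is plain Bonferroni for four comparisons, but the protocol also invokes the correlation between outcomes, and the choice of alpha is a separate question.

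**What to change.** Keep enrolment and the alpha of 0.017, and restate the power sentence by contrast. Suggested content:

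- With 87 per group analysed and before covariate adjustment, power is 90% for a difference of d = 0.56 between help sheet and detailed plan, and for d = 0.48 between the average of both tools and control. At d = 0.5 the first contrast has about 81%.
- If a gain from baseline adjustment is claimed, state the assumed correlation and the resulting power.
- Keep the f = 0.25, ~90% figure only for the 2-df omnibus and interaction tests, and name them.
- Replace the extension to all secondary analyses so that no ~90% power is claimed for the bootstrapped mediation analysis.

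The cost is a rewritten paragraph and a less favourable stated figure for the head-to-head comparison.

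### The alpha of 0.017 is labelled Bonferroni-adjusted for four comparisons, but Bonferroni gives 0.0125; using 0.017 for the four primary contrasts gives a familywise error of about 6.5%

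*Protocol*

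**What the plan says.** The sample size section of the Protocol gives the significance level as "assuming a Bonferroni-adjusted two-sided alpha of 0.017 (allowing for four planned comparisons" and "a correlation between the two primary outcome measures of ~ 0.25". On that basis, 87 analysed per group (261 in all) "will yield ~90% power to detect moderate effect sizes", with Cohen's f set at 0.25. It does not show how the number of comparisons and the correlation lead to 0.017.

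The count of four agrees with the rest of the document. The Primary Outcome section names two outcomes, maintenance self-efficacy and the unhealthy snacking score. The Hypotheses section sets out the same two comparisons for each. The section on data analysis says that "Orthogonal planned contrasts will be used to test if the volitional help sheet is superior to the detailed planning intervention", and goes on to the second contrast, the two planning tools against the passive control. Two contrasts on two outcomes make four tests. That section states no significance level, so 0.017 is the only one in the document.

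**The concern.** A Bonferroni level is the overall error rate divided by the number of tests. For four tests and the conventional 5% it is 0.0125, so the stated level does not match its own label and count. The level in use would be more lenient than the one named. A primary p-value between 0.0125 and 0.017 would be declared significant under an adjustment that does not support it, and the chance of at least one false positive among the primary tests would exceed the 5% that such an adjustment is meant to hold. The mention of a correlation raises the question whether 0.017 can be defended as a level adjusted for dependence, so that has to be checked as well.

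**Working it through.** **Inputs.** From the sample size section: alpha 0.017 two-sided, four comparisons, outcome correlation r of about 0.25, N = 261 in three equal groups, f = 0.25. From the data analysis section: two orthogonal contrasts per outcome. Assumptions: the overall target is 5%, and r = 0.25 is the correlation between the test statistics for the same contrast on the two outcomes.

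**1. The plan's own power.** The noncentrality is N × f² = 261 × 0.0625 = 16.31. For the 2-df group effect with 258 error df, the critical F at 0.017 is 4.14 and power is 90.35%. The smallest equal group size that reaches 90% is 87. The stated power and sample size therefore reproduce, on the 2-df test.

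**2. The level for four tests.**
- Bonferroni: 0.05/4 = 0.0125.
- Šidák: 1 − 0.95^(1/4) = 0.0127.
- Neither rounds to 0.017.

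**3. What the correlation can contribute.** Four tests form six pairs. Orthogonal contrasts in equal groups are uncorrelated, so r = 0.25 applies to only two of the six pairs: each contrast with itself across the two outcomes. The four tests fall into two independent pairs, and

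familywise error = 1 − P², where P = Pr(|Z₁| < c and |Z₂| < c) for a bivariate normal with correlation 0.25.

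| Per-test level | c | P | Familywise error |
|---|---|---|---|
| 0.017 | 2.387 | 0.96668 | 6.55% |
| 0.0125 | 2.498 | 0.97541 | 4.86% |

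Setting the error to 5% and solving gives a per-test level of 0.0129. For about 0.017 to hold 5%, the outcome correlation would have to be near 0.9 (0.0168 at r = 0.88, 0.0173 at r = 0.90).

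**4. Sensitivity of the 6.55%.** At 0.017 the Bonferroni bound is 4 × 0.017 = 6.8%, and independence gives 1 − 0.983⁴ = 6.63%. Even if all six pairs were correlated at 0.25, which the orthogonal contrasts rule out, the error would be 6.4%.

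**5. Where 0.017 might come from.**
- 0.05/3 = 0.0167, the Bonferroni level for three tests.
- A correlation-adjusted Bonferroni, 0.05/4^(1−r). At r = 0.25 this is 0.05/2.828 = 0.0177, and for r from just above 0.20 to 0.24 it rounds to 0.017. Four tests at 0.0177 have a familywise error of 6.8%. Using the mean correlation over all six pairs, 2 × 0.25/6 = 0.083, the same formula gives 0.0140.

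Neither route yields a level of 0.017 that holds 5%.

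**6. Power at 0.0125, f = 0.25.**

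| Test | N analysed | Power |
|---|---|---|
| 2-df group effect | 261 | 88.3% |
| 2-df group effect | 273 (91 per group) | 90.0% |
| 1-df contrast with its own f = 0.25 | 261 | 93.5% |

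**The case against.** The strongest defence is that the sample size section names both four comparisons and a correlation, which are the inputs of a correlation-adjusted Bonferroni. With a correlation given only approximately, that formula can land on 0.017. This stands as a plausible account of the figure, and it means a reader should not infer that the authors miscounted and divided by three. The document does not say which route was taken. It does not rescue the level, because the formula treats all the tests as sharing the correlation, which orthogonal contrasts do not.

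A second defence is that 0.017 is stated as a planning assumption, and that the data analysis section fixes no level. This also stands, as a condition: the 6.5% applies if 0.017 is carried into the primary tests. The mismatch between level, label and count is in the Protocol either way.

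A reader might also infer that the power is overstated. The document does not support that. The figure is right at the level stated, and at 0.0125 it falls by about two points on the 2-df test, against a claim that is itself approximate. For the 1-df contrasts that carry the hypotheses, power stays above 90% if f = 0.25 applies to each, though the Protocol does not say how f divides between them. The planned adjustment for baseline could add more. If f is on the unadjusted scale and baseline and follow-up correlate at 0.3 (an assumption, not a figure in the Protocol), 2-df power at 0.0125 is about 91.6%.

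**Conclusion.** Wrong as written, of moderate severity. The level of 0.017 is not the Bonferroni level for four comparisons, and a correlation of about 0.25 raises the permissible level only from 0.0125 to 0.0129. If the four primary contrasts are tested at 0.017, the familywise error is about 6.5% (6.4% to 6.8% across the dependence structures examined), an excess of about 1.5 points over 5%. This rests on a 5% overall target, on all four contrasts being tested at the stated level, and on the contrasts being orthogonal as the Protocol says. It does not depend on how 0.017 was obtained. The sample size and power calculation is sound at its stated alpha and needs restating only because the alpha changes.

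**What to change.** Set the two-sided level to 0.0125 for the four primary contrasts, or apply Holm's procedure to the four p-values, with 0.0125 for the smallest. Holm controls the same error and is never less powerful than Bonferroni. Delete the implication that the outcome correlation supports 0.017. If another adjustment was intended, name it and show that it holds 5% with two orthogonal contrasts on two outcomes. Settle this before outcome data are seen, so that the threshold cannot appear to follow the results.

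Restate the power at the corrected level and name the test: about 88% for the 2-df group effect with f = 0.25 and 261 analysed, or about 93.5% for a 1-df contrast if f = 0.25 is assumed for that contrast.

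The cost is Protocol wording and a slightly lower stated power on the 2-df test. Recruitment need not rise. If 90% is wanted on the 2-df test, 273 analysed would be needed, which is 273/435 = 63% of the planned recruits, against the 261/435 = 60% on which the present calculation rests.

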## Details of where the study will be undertaken (location/site/URL):

The online survey will be conducted via the Qualtrics website (www.qualtrics.com). Survey Sampling International (SSI) will send participants specific URLs to the survey. The University of Sydney will not make any direct contact with the participants.

## Details of how data will be collected:

Data will be collected directly from participants in the form of two online surveys. These will be spaced one-month apart. See the procedure below for further details as to data collection:

## Procedure:

### Participant recruitment and informed consent

Qualtrics will host the survey, and SSI will be used for recruitment of participants. Only SSI will have access to participant details (e.g. names and email addresses). Participants will be allocated an ID (provided to SSI) and this will be used to link baseline and follow up survey data. The data stored on Qualtrics’ server will therefore be de-identified and cannot be linked to participant details. SSI will not have access to the survey results as these are stored in the Qualtrics server in the specific the University of Sydney School of Public Health account used for this project. The investigators on this project are the only individuals with access to this account. The Qualtrics servers are protected by high-end firewall systems, secure data centres, and the company does not sell or make available specific information about participants except as required by law. This is outlined in the Qualtrics security statement and the Qualtrics privacy statement. Furthermore, the data that is stored on the Qualtrics server is de-identified (as stated above, participant contact details are only accessible to SSI).

Participants selected for this experiment will be men and women aged 30 years and older. Half of all participants will have no university degree. All participants will be required to be able to read and write in English. No other quotas or restrictions will be placed on participant recruitment. In other words, participants will be representative of the Australian community in terms of age, gender, socioeconomic status etc. The University of Sydney will not obtain any contact details from potential participants.

Initial contact will be made by SSI, who will use their database to approach potential participants who meet the eligibility criteria. Participants listed on their database have already indicated a willingness to participate in online research. If participants agree and are interested in being part of the study, they will be directed to an online Participant Information Statement, Consent Form, and then the surveys themselves.

Participants are free to withdraw from the study at any time. After reading the online Participant Information Statement, potential participants will be able elect to not proceed to the survey. It will be outlined in the Participation Information Statement that there will be no consequences to the individual should they wish to withdraw, and that they are able to withdraw from the survey at any point. In addition, participants who proceed to the survey and then discontinue survey completion part way through will be treated as though consent has been withdrawn, and their responses will not be used.

Participants will not receive any financial or other reward from the University of Sydney. SSI, the company that will be recruiting the participants, have a points-system whereby points are earned for completion of surveys. Specifically, points are based on survey length rather than being offered for particular surveys. These points can be redeemed for various items such as shopping vouchers and airline vouchers. The points represent modest compensation for the time that participants forgo by participating in the study. Participants will complete two surveys, 1 month apart. They will receive points on completion of the first survey and then more points again after completing the second survey. To be able to complete a survey and to collect the points, the respondent needs to quality for a survey, i.e. profile match and pass all quality checks. The value of the points in itself is not competitive with the minimum wage per hour, to avoid encouraging fake responses. This ensures that the completed surveys are quality-assured and less likely to be influenced by ‘incentives-skewed bias.

Participants will read an online Participant Information Statement followed by an online Consent Form. At the bottom of the Consent Form, participants will be asked “Do you consent”. They may click either ‘Yes’ or ‘No’. If participants click ‘Yes’ they will continue to the survey. If participants click ‘No’ they will not be able to continue to the survey. The University will only receive data from respondents that complete the surveys. To do so they have to have clicked ‘Yes’ at the Consent Form. Therefore, completing the survey will itself self as an indicator that they have consented (consistent with the NHMRC National Statement on Ethical Conduct in Human Research [2007]). Furthermore, participants, by virtue of being on the SSI database, have already consented to being involved in online research.

